### Statistical analyses

All data analyses will be performed after completion of data collection. Interim analysis is not considered necessary as in the context of IMIs, there are no known dangers or harms that could make a trial stop necessary. Analyses will be performed on an intention-to-treat basis. Procedures of imputation will be chosen based on patterns and mechanisms of missingness (e.g., by using multiple imputation). Additionally, per protocol analyses (based on the data of participants that completed at least 5 of the 7 core modules) will be performed to examine the impact of drop-outs on study results. Significance level for all analyses will be defined as alpha = .05. A blinded analysis of primary and secondary outcomes will be conducted by an independent researcher not otherwise involved in the execution of the study (MM).

The primary outcome FMI at t2 will be analyzed by means of linear regression models. Baseline and group will be defined as predictors. Secondary outcomes will be analyzed accordingly. Standardized mean differences with 95% confidence intervals will be calculated post-treatment and follow-up to analyze between-group effect sizes. To obtain the number of participants achieving reliable improvement in mindfulness (FMI), participants will be coded as responders and nonresponders according to the Reliable Change Index (RCI) for t2 and t3 [94]. Additionally, we will investigate potential negative effects on individual level by calculating the number of participants that display a reliable deterioration from t0 to t2 and t3 also using the RCI [95, 96]. For an exploratory examination of associations between adherence, subscription to SMS-coach, actual use of GoD, time spent practicing mindfulness exercises, and the primary outcome FMI at t2 regression analyses will be conducted.

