While unguided IMI formats can be effective, evidence suggests superior efficacy of guided IMI. In such guided IMIs, participants receive human support for working through the intervention, e.g., by an e-coach (health professional) giving them feedback and answering their questions. It has been proposed that the superior efficacy of guided IMIs might be due to increased intervention adherence [32]. Adherence is very relevant for mindfulness trainings, as mindfulness skills can only be developed with regular practice [18]. Indeed, unguided mindfulness IMIs have shown intervention dropout rates around 40–60% [29, 33, 34] and seem to be less efficacious then guided ones [25]. However, providing guidance also comes with increased intervention costs and therefore has implications for dissemination and scalability [25, 32]. These barriers might be overcome by using minimal guidance formats that combine the lower costs of unguided IMIs with the lower attrition rates of guided IMIs. One of these formats is called guidance on demand (GoD). In contrast to usual guidance formats, guidance by a therapist or e-coach will only take place when participants ask for it [32]. So far, only two trials examined GoD-IMIs, delivering cognitive behavioral therapy (CBT) to people with social phobia [35] and tinnitus [36]. Contrary to what one would expect, both studies did not find any significant differences in efficacy or adherence of GoD-IMIs compared to unguided IMIs. However, the social phobia trial [35] also found no differences between the GoD and a guided version nor the guided and an unguided version, which is somewhat surprising considering previous evidence for the superiority of guided IMIs [25]. Those results might be explainable by the fact that samples in both trials were highly burdened and therefore very motivated, irrespective of guidance [36]. In line with this, intervention dropout in the two studies was rather low and comparable in all conditions (20–30%). It remains to be examined whether these results can be generalized to mindfulness IMIs designed for non-clinical target-groups typically showing lower adherence.

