## Methods

### Study design

This multicenter, three-armed randomized controlled trial of parallel design compares the efficacy of an unguided (UG) as well as a “guidance on demand” (GoD) version of the internet-based, preventive intervention *StudiCare Mindfulness* (StudiCare-M) to a waitlist control group (WL) receiving no intervention (superiority trial; see Fig. 1 for flowchart) within the framework of the StudiCare project funded by BARMER [45]. StudiCare dedicates itself to examining and promoting college students’ well-being offering a broad assortment of internet-based interventions for psychological and behavioral issues (e.g., procrastination, test anxiety, physical activity, depression, substance use, stress [20, 46–50]. It is embedded in the “World Mental Health Survey International College Student” project (WMH-ICS) [51] as well as the “Caring Universities” project [52].

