#### Control condition

Participants in the waitlist control group have unrestricted access to usual treatment options (TAU). They receive an information leaflet informing them about alternative support options such as university counseling services, psychotherapy, or helplines as well as the encouragement to seek help in case of any deterioration of wellbeing. After t3 (6 months after randomization), WL participants receive the unguided version of the intervention.

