##### Intervention satisfaction and adherence

The Client Satisfaction Questionnaire (CSQ-8) [79] is a validated 8-item instrument and is used in a version adapted for the evaluation of IMIs [80]. It comprises of eight items, each with a 4-point scale of specific response alternatives (e.g., 1 = “quite unsatisfied,” 4 = “very satisfied”). Good psychometric properties have been demonstrated including Cronbach’s *α* between .88 and .92 [81]. To operationalize intervention adherence, the number of completed modules is assessed. “Per protocol” adherence is operationalized by the percentage of participants that completed at least 5 of the 7 modules 8 weeks after randomization (t2). Additionally, quantitative and qualitative data are collected on participants’ satisfaction with various aspects of the intervention (e.g., number and length of modules, SMS-Coach, practicability in daily life) using self-constructed items (e.g., “Which elements did you find particularly helpful?”).

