### Sample size estimation

Sample size calculations refer to detect an expected increased efficacy of StudiCare-M unguided and GoD compared to WL on the primary outcome mindfulness at t2 (post-treatment). In their meta-analysis, Spijkerman et al. (2015) found a small effect for unguided mindfulness IMIs (*g* = 0.22, 95% CI 0.10–0.34) and a significantly larger effect for guided IMIs (*g* = 0.43, 95% CI 0.30–0.56) [25]. The GoD version of our IMI provides the possibility to contact an e-coach at any time. Additionally, both the GoD and unguided versions contain various persuasive e-health technologies and that have been shown to increase efficacy and adherence (e.g., self-monitoring, goal setting, SMS prompts, automatic reminders) [63, 92]. Therefore, we assume an effect size comparable to the effects previously found for guided IMIs of *d* = 0.40. Originally, a power analysis based on a two-tailed t-test (calculated using G*Power [93]) resulted in a sample size of 133 participants per group. This was documented in the first version of the trial registration. However, in the meantime, a more precise power calculation was done by an independent biostatistician (MM). This calculation indicates that 129 participants per group are required to obtain a power of 1-beta = 90% based on *α* = .05 (taking into account clustering of participants by university and assuming an ICC = .02). Trial registration was updated accordingly. As data analysis will be based on intention-to-treat (ITT) principles, increasing sample size in order to compensate for drop-outs is not necessary.

Concerning an exploratory comparison between the UG and GoD version of StudiCare-M, the sample size is sufficient to detect a small effect of *d* = 0.20 as minimal clinically important effect difference with a power of 50% and a significance level of *α* = .05. This also corresponds to the range of effect sizes of *d* = 0.02–0.33 found for different outcome measures in the trials of Berger et al. [35] and Rheker et al. [36].

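### The supplementary per-protocol set is defined by module completion, which no waitlist participant can reach before t3, so it has either no control arm or a self-selected comparison

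*Protocol article*

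**What the plan says.** The Statistical analyses section makes ITT the main basis and adds that "per protocol analyses (based on the data of participants that completed at least 5 of the 7 core modules) will be performed", the aim being "to examine the impact of drop-outs on study results". It gives no separate rule for the waitlist. The section on intervention satisfaction and adherence uses the same threshold and fixes the time at which it is judged: "completed at least 5 of the 7 modules 8 weeks after randomization (t2").

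The control arm is described under Study design as a comparison "to a waitlist control group (WL) receiving no intervention", and the Control condition section says: "After t3 (6 months after randomization), WL participants receive the unguided version of the intervention". The sample size refers to the "expected increased efficacy of StudiCare-M unguided and GoD compared to WL on the primary outcome mindfulness at t2 (post-treatment"). For the regression model, "Baseline and group will be defined as predictors"; no other covariate is named. One significance level of .05 is set for all analyses.

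**The concern.** A per-protocol set has to say who counts as adherent in every arm that enters the comparison. Here the only criterion is module completion, and one of the three arms has no modules during the whole assessment period.

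The analysis can then be read in two ways, and neither supports a causal statement about adherence. On the literal reading, neither active-versus-WL contrast can be estimated. On the reading that keeps WL whole, the active arms are cut down by a behaviour that occurs after randomisation and the waitlist is not. If completers differ from non-completers in ways that baseline FMI does not capture, that difference goes into the estimated effect. The UG versus GoD contrast among completers has a related problem: on-demand guidance is meant partly to change who completes.

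The risk lies in interpretation. A completer-versus-WL estimate larger than the ITT estimate could be reported at the .05 level as what the programme achieves in those who follow it, when part or all of the excess is selection.

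**Working it through.** **Step 1: can a WL participant enter the set?** The rule needs at least 5 completed modules, judged at t2 (8 weeks). WL access begins after t3 (6 months). The number of WL participants who can qualify at t2 or t3 is therefore 0 of the planned 129.

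**Step 2: what is left on the literal reading.** Earlier trials are the protocol's only guide to completion. The Introduction says that "unguided mindfulness IMIs have shown intervention dropout rates around 40–60"%, so completion would be about 40 to 60%. That leaves 129 × 0.4 ≈ 52 to 129 × 0.6 ≈ 77 per active arm and no controls.

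**Step 3: what happens if all WL are kept.** Let *c* be the share who complete and *g* the mean prognosis of completers minus that of non-completers, in residual SD after adjustment for baseline FMI. With no treatment effect, randomisation makes the whole active arm equal to WL on average. So:

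- apparent effect = *g* × (1 − *c*)
- SE = √(1/(129*c*) + 1/129), in residual SD
- false-positive rate = Φ(*z* − 1.96) + Φ(−*z* − 1.96), with *z* = apparent effect / SE

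Inputs: 129 per group is from the Sample size estimation section. It can be reproduced for *d* = 0.40, 90% power and two-sided .05 if the variance is multiplied by 1 − ICC = 0.98: 2 × (1.960 + 1.282)² × 0.98 / 0.40² = 128.7, rounded up to 129. The values of *g* are assumptions; the documents give none. Completion of 40 to 60% comes from the dropout range above. Completion of 70 to 80% corresponds to the 20–30% dropout that the Introduction reports for the two earlier GoD trials.

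Worked case, *g* = 0.3 and *c* = 0.5: apparent effect 0.3 × 0.5 = 0.15 SD; SE = √(1/64.5 + 1/129) = 0.1525; *z* = 0.984; false-positive rate = 0.164 + 0.002 = 0.166.

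| Gap *g* (assumed) | Completion *c* | Apparent effect under no effect | SE | False-positive rate |
|---|---|---|---|---|
| 0.1 | 50% | 0.05 | 0.152 | 6% |
| 0.3 | 80% | 0.06 | 0.132 | 7% |
| 0.2 | 60% | 0.08 | 0.144 | 9% |
| 0.3 | 70% | 0.09 | 0.137 | 10% |
| 0.3 | 50% | 0.15 | 0.152 | 17% |
| 0.4 | 40% | 0.24 | 0.165 | 31% |

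With *g* = 0 there is no bias and the rate is 5%. With *g* negative the apparent effect has the same size in the other direction, and the analysis understates benefit.

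**The case against.** **The literal reading is strained.** The protocol uses per protocol as a measure of intervention adherence, which exists only in UG and GoD. A reasonable analyst would apply the rule there and keep WL, and a condensed article may leave that detail to the statistical analysis plan. This is fair as to what was probably meant. It does not remove the problem, because keeping all WL is exactly the reading that produces a non-randomised contrast in a model with only baseline and group.

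**The analysis is supplementary.** This stands. ITT is the main analysis, and the UG versus GoD comparison is already exploratory. A reader might infer that the trial's type I error is inflated; the documents do not support that. The rates above belong only to the completer contrast.

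**The inputs are chosen.** This also stands. No passage gives the gap or its sign. The protocol suggests that participants in the earlier GoD trials were highly burdened and therefore motivated, so completers need not have the better prognosis. Reminders and the SMS coach may raise completion, which shrinks the bias.

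**The set does serve its stated aim.** A reader might infer that a module-based set cannot examine drop-outs because it ignores missing assessments. That does not hold. Table 2 operationalises adherence as intervention dropout, and the Discussion deals with assessment dropout through ITT. Intervention dropout is therefore the natural meaning, and a set defined by modules addresses it.

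**An instrumental-variable analysis has weaknesses of its own.** It does, and they are set out with the fix.

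**Conclusion.** The concern holds for the supplementary per-protocol analysis and goes no further. That no WL participant can meet the rule before t3 follows from the protocol's text alone. So does the conclusion that the alternative reading compares completers selected after randomisation with an unselected arm. The ITT result is untouched.

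The size is illustrative. In the central case a null effect appears as 0.15 SD, which is 0.15/0.40 = 38% of the planned *d* = 0.40, with about 17% false positives. Across the inputs shown, the rate runs from about 6% to 31%. These figures assume that completers have the better prognosis after baseline adjustment, and that all 129 WL participants and all completers are analysed. It would be wrong to conclude that the analysis must overstate benefit: the direction depends on the sign of an unknown gap. The conclusion is that the analysis cannot tell adherence from selection.

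**What to change.** 1. State that the module rule applies to UG and GoD only, and how WL enters.
2. Label the completer-versus-WL and the UG-versus-GoD completer contrasts descriptive and non-randomised. They may stay on those terms.
3. Base any claim about the effect of adhering on a complier average causal effect for each active arm versus WL, in all randomised participants: two-stage least squares with randomised arm as instrument, at least 5 modules by t2 as exposure and baseline FMI as covariate. Because WL cannot obtain the modules before t3, non-compliance is one-sided by design. Add the number of modules completed (0 to 7) as a sensitivity exposure.

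The cost is small, since modules completed and baseline FMI are already collected. The protocol is dated 23 October 2020, data collection was due to end in November 2020 and analyses follow it, so the change could still be prespecified at this version.

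The downsides should be stated with the result:

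- Intervals widen by about 1/completion: 1/0.6 = 1.7 to 1/0.4 = 2.5 times at 60 to 40% completion.
- The test is essentially the ITT test rescaled, so it adds an estimate and no new evidence of efficacy.
- The exclusion restriction requires that assignment does nothing for non-completers. If 1 to 4 modules, SMS prompts or e-coach contact help them, the complier effect is overstated.
- The module-count version eases this for partial module use only, and assumes a linear dose effect instead.

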**Discussion:**

Providing effective interventions to help college students become more resilient can make a valuable contribution to the health and functionality of future society. If effective under the condition of minimal or no guidance, StudiCare-M offers a low-threshold potentially resource-efficient possibility to enhance college student mental health on a population level. Moderation- and mediation analyses will deliver further insights for optimization of target groups and intervention content.

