Finally, the questions of how and for whom exactly mindfulness-based IMIs (as well as IMIs in general) work are yet to be answered [25, 37]. As large-scale RCTs provide an excellent framework for moderation and mediation analyses, they should routinely incorporate such analyses [38]. Therefore, in the current study, we will exploratively examine various potential moderating variables such as sociodemographic variables, pre-treatment symptomatology and treatment expectancy. From theory and current evidence, we also deduced a number of potential variables mediating the effect of mindfulness IMIs on mental health. Those include mindfulness itself [39], cognitive fusion as an aspect of psychological flexibility [39, 40], emotion regulation [41] and clarity about one’s internal experience (operationalized via alexithymia) [42]. Additionally, we will look at self-efficacy, as empowerment and self-management are assumed to be crucial factors for the efficacy of self-help interventions [43].

The current study is an extension of a previous RCT that investigated the efficacy and acceptance of *StudiCare Mindfulness* (StudiCare-M), a guided internet-based intervention to enhance mindfulness and wellbeing in college students [44]. We will examine whether an adapted unguided as well as a GoD version can be effective, as these would offer affordable options for long-term implementation into student health promotion programs. The specific research questions are:
Are the unguided and GoD versions of StudiCare-M effective in enhancing mindfulness in college students compared to a waitlist control group?Are these two versions also effective concerning the secondary outcomes depression, anxiety, stress, presenteeism, well-being and interoceptive sensibility?Are the unguided and GoD versions of StudiCare-M associated with side effects or adverse events?Are there any differences between the unguided and GoD version of StudiCare-M concerning efficacy, adherence, satisfaction, side effects, or adverse events?Which factors are associated with, moderate or mediate the effects of StudiCare-M?

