**Fig. 1 Fig1:**
[figure not shown]
Flow diagram

The two versions of StudiCare-M are further compared to each other on an exploratory level to gain insights on potential differences in effectiveness, adherence, satisfaction side effects, and adverse events. Participants in all intervention arms are informed about and have access to treatment as usual. Use of other support options is monitored to control for potential confounding effects. The present study is conducted and will be reported according to the CONSORT 2010 Statement [53] and the guidelines for executing and reporting internet intervention research [54]. The study protocol follows recommendations of the SPIRIT 2013 Checklist for clinical trial protocols [55].

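### No multiplicity rule is given for the two primary comparisons against the shared waitlist; at two-sided .05 each, the familywise type I error is about 9.1%, and the chance of a false finding of benefit is about 4.5% instead of 2.5%

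*Protocol article*

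**What the plan says.** All statements are in the protocol article.

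- **Research question** (Introduction): the first question covers both versions together, "Are the unguided and GoD versions of StudiCare-M effective in enhancing mindfulness in college students compared to a waitlist control group".
- **Powered comparisons** (Sample size estimation): the calculation concerns "expected increased efficacy of StudiCare-M unguided and GoD compared to WL on the primary outcome mindfulness at t2". The result is 129 per group for 90% power at alpha .05, allowing for clustering by university with ICC .02. It replaces an earlier figure of 133 per group.
- **Primary model** (Statistical analyses): linear regression of FMI at t2, for which "Baseline and group will be defined as predictors". The contrasts are not written out.
- **Error rate** (Statistical analyses): "Significance level for all analyses will be defined as alpha = .05".
- **UG against GoD** (Study design): the two versions are "further compared to each other on an exploratory level", so this comparison is outside the primary set.
- **Conclusion to be drawn** (Discussion part of the Abstract, repeated in the last paragraph of the Discussion): "If effective under the condition of minimal or no guidance, StudiCare-M offers a low-threshold potentially resource-efficient possibility".

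**The concern.** Two confirmatory contrasts remain: GoD vs WL and UG vs WL on FMI at t2. They share an outcome, a time point and a control arm, and they test two versions of one seven-module intervention. The closing statement is about a single product and joins the two conditions with an 'or', so a significant result in either arm could be used to support it.

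Two chances of success at .05 each give more than a 5% chance of at least one false positive. If no rule is set before the data are seen, the reported .05 is not the error rate of the overall conclusion. It is also left open how a split result, with one arm significant and the other not, would be reported.

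**Working it through.** **Inputs**

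- d = 0.40, power 90%, alpha .05, ICC .02, 129 per group (Sample size estimation).
- Two-sided testing. The article states this for the 133 figure, "a power analysis based on a two-tailed t-test". It does not repeat it for the 129.
- Allocation 1:1:1 (Randomization).
- An effect of g = 0.22 for unguided mindfulness interventions, from the meta-analysis cited under Sample size estimation.

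**1. Reproducing the planned sample size**

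n per group = 2 × ((1.960 + 1.282) / 0.40)² = 131.3, so 132 by the normal approximation. The exact t calculation gives 133 (power 0.9015), which is the earlier figure.

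With individual randomisation within universities, the between-university variance drops out and the residual variance is multiplied by 1 − ICC: 131.3 × 0.98 = 128.7, so **129**. The article does not print this formula, but the result matches exactly. Alternatives do not match:

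| Assumption | n per group |
|---|---|
| One-sided .05 (without ICC factor) | 108 |
| Bonferroni, .025 per comparison (with ICC factor) | 153 |
| Dunnett, .027 per comparison (with ICC factor) | 150 |

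The design figure therefore implies an unadjusted two-sided .05 for each comparison.

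**2. Type I error with two tests at .05**

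With equal arms of size n, each contrast has variance 2σ²/n, and the two share the waitlist mean with variance σ²/n. Their correlation is therefore (σ²/n) / (2σ²/n) = 0.5. For a bivariate normal pair with correlation 0.5 and no effect in either arm:

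| Event | Two tests | Single test |
|---|---|---|
| Any false difference: P(max of the absolute Z values > 1.96) | 9.07% | 5% |
| False finding of benefit in at least one arm: P(max Z > 1.96) | 4.54% | 2.5% |
| Both contrasts significant | 0.9% | – |

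Simulation agrees with the first row (9.07%). For comparison, independent tests would give 1 − 0.95² = 9.75%, and the Bonferroni bound is 10%. On either convention the error is about 1.8 times that of one test (9.07/5 and 4.54/2.5).

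**3. Power at 129 per group under a rule**

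With the ICC factor, the expected Z for d = 0.40 is 0.40 × √(129/2) / √0.98 = 3.245. Unadjusted power is Φ(3.245 − 1.960) = 90.1%.

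| Rule | True effects | Power |
|---|---|---|
| Unadjusted | 0.40 | 90.1% per comparison |
| Holm | both 0.40 | 88.3% per comparison |
| Holm | GoD 0.40, UG 0.22 | 84.9% for GoD |
| Fixed order, GoD then UG | both 0.40 | 90.1% for GoD, 83.4% for UG |
| Bonferroni | 0.40 | 84.2% per comparison |
| Dunnett, single step | 0.40 | 84.9% per comparison |

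The UG figure under the fixed order is the probability that both contrasts exceed 1.96. Under the full null, Holm rejects at least once exactly when Bonferroni does, in about 4.7% of trials.

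**The case against.** **The two versions may be separate questions.** The Introduction and the sample size section name both versions, and the Discussion asks about GoD in its own right. If each version carries its own claim, testing each at .05 is a recognised, though contested, position. This stands in part: the article never defines a formal success rule, and the either-arm reading is inferred from the wording of its conclusion. But the article does not argue for separate claims either, and its closing sentence speaks of one product.

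**Separate tests at .05 are themselves inferred.** The contrasts are not written out. A global two-degree-of-freedom test of group before the contrasts would hold the error at about 4.2% under the full null, and a full protocol or analysis plan that is not shown may contain such a rule. A sample size calculation does not fix a test procedure. This stands as a caveat. Still, the article sets one level for every analysis and mentions no gate, and its sample size fits unadjusted tests.

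**Two stronger readings are not supported.**

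- A reader might infer a 9% chance of a false efficacy claim. The 9.1% includes false findings that the intervention is worse than waitlist. The rate for false benefit is about 4.5%.
- A reader might also extend the criticism to the secondary, moderator and mediator tests. The article names one primary outcome at one time point, places the other outcomes under a secondary heading, and describes the moderator, mediator and UG-versus-GoD analyses as exploratory. Unadjusted secondary outcomes are ordinary practice.

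**Conclusion.** The point holds for the two primary contrasts only. Following the article as written, with each contrast at two-sided .05, gives a familywise type I error of about 9.1% for any false difference and about 4.5% for a false finding of benefit in at least one arm, against 5% and 2.5% for a single test.

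This assumes equal arms, approximately normal test statistics, no effect in either arm, no preceding global test, and that the two contrasts form one family. The last two assumptions are inferred from the text.

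The design remains sound. This is a cheap improvement, and it does not undermine the trial.

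**What to change.** Add to Statistical analyses: 'The two primary contrasts, GoD vs WL and UG vs WL on FMI at t2, are tested with the Holm procedure at a familywise two-sided alpha of .05.' Alternatively, pre-specify a fixed order, GoD then UG, each at two-sided .05, with UG tested confirmatorily only if GoD is significant. Then restate the power in Sample size estimation under the chosen rule.

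**Cost.** No additional participants are needed.

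- Holm costs about 2 percentage points of power per comparison if both effects are 0.40 (88% instead of 90%). It costs GoD about 5 points (85%) if the UG effect is 0.22. The smaller figure should not be quoted without its condition, because the assumption for both arms, "we assume an effect size comparable to the effects previously found for guided IMIs of *d* = 0.40", is taken from guided interventions.
- The fixed order costs GoD nothing. UG then has about 83% power if both effects are 0.40, and no confirmatory claim for UG is possible if GoD fails.

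**Timing.** The article places all analyses after data collection and, as amended in October 2020, expects collection to end in November 2020. On those dates, the rule could still be fixed before the blinded analysis.
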